# A five-year randomized parallel and blinded clinical trial of an extended specialized early intervention vs. regular care in the early phase of psychotic disorders: study protocol

**DOI:** 10.1186/s12888-015-0404-2

**Published:** 2015-02-14

**Keywords:** Specialized early intervention, First episode psychosis, Treatment, Critical period, Remission, Case management, Randomized controlled trial

## Abstract

**Background:**

Specialized Early Intervention services (SEI) for first episode psychosis are shown to be effective for the treatment of positive and negative symptoms, medication adherence, rates of relapse, substance abuse disorders, functional outcome and quality of life at two-year treatment follow up. However, it is also reported that these benefits are not maintained when SEI is not sustained. The objective of this trial is to test the efficacy of a 3-year extension of a SEI service (following 2 years of SEI prior to randomization) for the maintenance and consolidation of therapeutic gains as compared to regular care in the community.

**Methods:**

Following an initial 2 years of SEI, patients are randomized to receive either 3-years of continued SEI or regular care. SEI provided at three sites within the McGill network of SEI services, using a model of treatment comprised of: modified assertive case management; psycho education for families; multiple family intervention; cognitive behavioural therapy; and substance abuse treatment and monitoring. Blinded research assistants conduct ongoing evaluation of the outcome variables every three months. The primary outcome measure is remission status measured both as the proportion of patients in complete remission and the mean length of remission achieved following randomization during the additional three years of follow up. Based on preliminary data, it is determined that a total of 212 patients are needed to achieve adequate statistical power. Intent to treat with the last observation carried forward will be the primary method of statistical analysis.

**Discussion:**

The “critical period” hypothesis posits that there is a five year window during which the effects of the nascent psychotic illness can be countered and the impact of the disorder on symptomatic and functional outcomes can be offset through active and sustained treatment. Providing SEI throughout this critical period may solidify the benefits of treatment such that gains may be more sustainable over time as compared to intervention delivered for a shorter period. Findings from this study will have implications for service provision in first episode psychosis.

**Trial registration:**

ISRCTN11889976

## Background

Psychotic disorders including schizophrenia spectrum and affective psychosis are considered among the most severe mental disorders [1], resulting in personal and family suffering [2,3] and associated with poor long term outcomes, particularly if not adequately treated [4-6]. The first episode of psychosis (FEP) typically occurs between adolescence and early adulthood [7] and interferes with educational and employment attainment as well as social transitions [8]. The life time prevalence of all psychotic disorders, that include the presence of at least one positive symptom, is up to 3.4% in the general population [9]. In Canada alone, the overall economic cost to society that includes loss of productivity as a result of psychosis is estimated at over six billion dollars per year [10].

While most patients will respond positively to initial treatment [11], the long-term prognosis is varied [12]. Only up to one quarter of all psychosis patients are likely to achieve complete remission, depending on the criteria and length of follow up applied [12,13]. Given such likely negative outcomes, emphasis has been placed on the earliest phase of psychosis, considered a “critical period” of five years [14] when patients’ psychosocial health may otherwise be most likely to decline [15] unless long term health trajectories are re-established [16]. Specialized Early Intervention (SEI) programs were first initiated in the 1990s as a response to mounting evidence of the importance of prevention, early detection and appropriately targeted and timely treatment during this critical period [17].

In comparison to regular care where the majority of patients (80%) fail to sustain remission within the first five years [18,19], FEP patients treated in an SEI model, show higher rates of remission, lower rates of residual positive and negative symptoms, lowered rates of relapse, less substance abuse and better overall functioning at one and at two years [11,20-24]. Indeed, the benefits of SEI service as compared to treatment as usual over the short term have been verified by three randomized controlled trials [25-28] as well as uncontrolled studies (for a meta-analytic review see Harvey et al., 2007 [29]). Despite such encouraging outcomes, a five year uncontrolled study of FEP patients treated for 12 months in an SEI service and then transferred into regular care showed a loss of the beneficial effects achieved earlier in treatment [30]. Critically, in a five year follow up study (OPUS Trial) of a large sample of FEP patients, who had received two years of SEI service before being transferred to regular care, the therapeutic gains achieved at two years were not maintained over the following three years [31].

This loss of advantage seen over the subsequent three years during which SEI services were no longer available may have been prevented if the SEI service were continued throughout the critical five-year period in FEP. In a recent study conducted in Canada, a reduced level of SEI service was offered to all patients for three years beyond the standard first two years of SEI treatment [32]. Although there was no comparison group and the intensity of SEI was lowered, patient outcome data after five years (two years of SEI followed by three years of stepped down SEI) when compared to the five-year outcome data of OPUS patients who had only received two years of SEI treatment were significantly better (rates of remission and hospitalization) [32].

Based on the evidence reviewed above, the current study is being conducted to address this question of optimum treatment length using a randomized controlled (RCT) design at the Prevention and Early Intervention Program for Psychosis (PEPP-Montreal). In this RCT we evaluate the effect of three years of extension of full SEI services following two years of SEI, compared to three years of regular care following the initial two years of SEI service.

The **primary hypothesis** guiding this RCT is that individuals in the experimental group (extended SEI) will show higher rates and longer periods of remission (both positive and negative symptoms) than the control group over the extension period of three years. The *secondary hypotheses* are that: a) the difference in remission rates are mediated by the level of medication adherence in the two groups; b) as the experimental group is expected to have higher levels of working alliance with their treatment providers than the control group, we hypothesize that the difference in the level of medication adherence between the two groups and retention in treatment is predicted by working alliance; c) that the experimental group will have better clinical outcomes (lower relapse rates and levels of symptoms), functional outcomes (social/occupational functioning), and quality of life than the control group. The economic consequences of extending SEI past the standard current 2 years is also being investigated, within the RCT design, taking into consideration both direct and indirect costs.

## Methods

### Design

This trial is a randomized controlled trial comparing extended SEI for FEP (five years total) with treatment as usual for FEP (two years of SEI followed by three years of regular care). Prior to randomization, all patients received their treatment from the McGill University network of hospitals that offer SEI service according to a common model of care within a defined catchment area in the city of Montreal.

### Inclusion criteria

Our aim is to use inclusion criteria that are as non discriminatory as possible in order to ensure the ecological validity of this trial and to reflect the kinds of diverse patients seen in FEP clinical settings. Although the SEI services treat patients between 14 and 35 years old, for the purpose of the study, patients aged 18–35, with a DSM-IV diagnosis of a psychotic disorder (schizophrenia spectrum psychoses and affective psychosis), who have completed two years of SEI treatment and follow-up within the McGill network of SEI services, an IQ greater than 70, the ability to communicate in either French or English, and the ability to provide informed consent, are eligible for participation. Patients are recruited regardless of their remission status at the end of two years of SEI treatment, consistent with what may be seen in regular clinical practice. Ethics approval for this RCT was granted by McGill University’s Faculty of Medicine Institutional Review Board (Assurance number: FWA 00004545) and from the Douglas Hospital Research Ethics Board.

### Exclusion criteria

Patients who are not able to provide informed consent (as determined by an inability to provide a brief summary of the treatment protocol following presentation of the consent form); those with an inability to communicate in either English or French; and those with an I.Q. below 70 are ineligible for participation. Co-morbid substance abuse and dependence is not an exclusion criteria.

### Randomization

Randomization is stratified according to sex and substance abuse to ensure that these two factors, know to influence outcome, are balanced between groups. Once participants have signed informed consent to be randomized, their initials and ID # are given to an on site statistician who is not connected with the service. Randomization to one of the two treatment conditions is conducted using a computerized urn randomization protocol [33]. Post-randomization, patients are asked which condition they would have preferred to be randomized to and if they are satisfied with the allocation they were assigned. Results of the randomization are communicated to the treatment team such that appropriate transfer decisions may be made, in the case that a patient is randomized to regular care. This data will be used as a covariate in case that treatment preference biases outcomes (Figure 1).

**Figure 1 Fig1:**
[figure not shown]
**Diagram of study participants in PEPP trial of extended SEI.**

### Recruitment

Patients who have received ongoing modified case management for the entire two-year period are screened for their participation. Patients that meet the inclusion criteria are approached for their participation between months 21 and 24 of SEI from one of the three McGill network SEI sites. The principal site of recruitment is the Prevention and Early Intervention Program for Psychosis (PEPP-Montreal), established in 2003 and the largest of the three sites; FEP Program at the Jewish General Hospital (established in 2007) and the PEPP at the McGill University Health Centre (established in 2009).

### Participants

#### Blinding

Neither the participants nor case managers and other clinicians can be blinded to the assignment of the treatment condition. However, trained research staff, not involved in the patients’ care and blinded to the treatment condition, conduct all assessments outside any of the patient treatment facilities. Baseline assessments are conducted as soon as possible, within the first 3-6weeks of randomization, in order to avoid revealing group assignment. This is done to prevent any possibility of bias in self-reports that could influence the comparability between groups. In cases where the blind is broken, additional analyses, excluding the unblinded cases, will be conducted to test for any effect of unblinding.

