
#### The control intervention

Patients randomized to the control condition receive treatment as usual in general medical or regular psychiatric services that are available for free to all Quebec patients. Primary regular care in Quebec is predominantly offered through local health and community services centres (CLSCs) that provide health and social services to their catchment area. Care by a family physician in the community is provided in a variety of settings, including at CLSCs and private clinics, and is of variable quality and intensity. Secondary (psychiatric) regular care, including hospital in- and out-patient services, offer a range of psychosocial rehabilitation services, that are part of regular care available to all patients randomized to the control condition.

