**Table 1 Tab1:** **Assessment instruments**

**Assessment**	**Instrument**
Psychopathology	Scale for the Assessment of Positive Symptoms (SAPS) [41]*
	Scale for the Assessment Negative Symptoms (SANS) [42]*
	Positive and Negative Syndrome Scale (PANSS) [43]*
	Brief Psychiatric Rating Scale (BPRS) [44]*
Functioning	Global Assessment of Functioning Scale (GAF) [45]*
	Social and Occupational Functioning Scale (SOFAS) [46]**
	Productivity Interview Questionnaire (adapted from the Client Socio-Demographic and Service Receipt Inventory) [47]*
	Life Skills Profile [48]**
Medication and side effects	Patient Compliance Interview [49]*
	Medication Compliance: Pill Count Form [49,50]*
Substance use	Chemical Use/Abuse/Dependence-Scale (CUAD) [51]*
	Time Line Follow Back [40]*
Working alliance	Working Alliance Inventory (WAI) [52]**
Randomization preference	Self administered questionnaire***
Quality of life	Life Satisfaction and Psychological Well-being domains of the Wisconsin Quality of Life-Client version [53]**
Duration of untreated psychosis	Circumstances of Onset and Relapse Schedule (CORS) [11]***
Promorbid adjustment	Premorbid Adjustment Scale (PAS) [52]***
Service use including hospital admittance and total bed days	Self administered questionnaire with list of services received
	Regie de l’Assurance-maladie du Quebec (Quebec medical insurance; RAMQ)****
	Med-Echo (for hospitalizations)****

*Assessed at each evaluation (every 3 months).

**Assessed at every second evaluation (every 6 months).

***Assessed once at baseline.

****Assessed post study completion.

Data on the Duration of Untreated Psychosis (DUP) are available for all PEPP patients and is derived using the Circumstances of Onset and Relapse Schedule (CORS) [11], a structured interview instrument for use with patients and families that includes some sections from the Interview for the Retrospective Assessment of Onset of Schizophrenia (IRAOS) [54]. DUP data for all other patients is available through chart verification.

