### Primary outcome

The primary outcome is complete remission measured as both the proportion of patients in remission, as well as the mean length of remission achieved following randomization during the additional three years of follow up. Complete remission is defined according to consensus criteria as a rating of mild or less on the following positive and negative symptom scale items (Positive domain: hallucinations, delusions, bizarre behaviour, positive formal thought disorder; Negative domain: affective flattening or blunting; alogia; avolition-apathy; anhedonia-asociality) for a period of six months [55]. Complete remission is chosen as the primary outcome measure as per findings that remission across both symptom domains is a better predictor of functional outcome than remission of positive symptoms alone [56,57]. Remission is measured at each assessment covering the three months prior using the Scale for Assessment of Positive Symptoms [41] and the Scale for the Assessment of Negative Symptoms [42]. The SANS domain of Attention is not included in SANS ratings as these items have not been shown to correlate to the domain of negative symptoms [58].

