A limitation of any service based trial is that we are unable to blind participants or service providers to treatment allocation. While participants may not receive their preferred allocation in either condition, this possibility is discussed beforehand. That assessors are independent of treatment providers and conduct their evaluations blind to the treatment allocation outside of the patients’ treatment location will reduce chances of unblinding the treatment assignment and ensure the integrity of symptom and functional assessments.

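### The off-site assessment rule has no in-patient provision and, with last observation carried forward, can let a psychosis admission be filled with an earlier remission rating

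*Protocol article*

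**What the plan says.** - **Place of assessment.** Protocol article, Blinding: research staff outside the care team "conduct all assessments outside any of the patient treatment facilities". No in-patient exception is printed. The Discussion returns to this more loosely: assessors "conduct their evaluations blind to the treatment allocation outside of the patients", with the sentence going on to name the treatment location. It says that this "will reduce chances of unblinding the treatment assignment and ensure the integrity of symptom and functional assessments". The purpose is therefore protection of the blind.
- **Hospital as a place of treatment.** The control intervention: "Secondary (psychiatric) regular care, including hospital in- and out-patient services" belong to regular care, so a ward is naturally read as a treatment facility.
- **Rating window.** Primary outcome: "Remission is measured at each assessment covering the three months prior". Complete remission requires ratings of mild or less "for a period of six months", which is two consecutive three-month windows.
- **Missing data.** Abstract, Methods: "Intent to treat with the last observation carried forward will be the primary method of statistical analysis". Statistical analyses does not mention LOCF. It provides selection and pattern-mixture models as robustness checks if missingness is judged non-ignorable.
- **Admissions.** Table 1 and Economic analysis obtain hospital stays from Med-Echo. Secondary outcomes uses admission in the definition of relapse. No section links admissions to remission.

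**The concern.** Each of the two rules is reasonable alone. Off-site rating protects the blind, and an imputation rule is needed for missed visits. Together they leave a gap exactly where the primary outcome is most likely to be negative. If a patient relapses, is in hospital on the visit date and is not rated, LOCF can supply the last status, which may be remission. The missing value is then related to the outcome itself.

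Both primary measures are exposed. A genuine remission window followed by one carried across an admission can complete the six months, and the length of remission can be credited with time spent ill.

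The document gives reason to expect a difference between arms. The experimental intervention aims at less reliance on hospital services, and the Background reports better hospitalization results for a cohort with extended early intervention than for patients returned to regular care. If that holds here, control remission is inflated more and the treatment difference shrinks.

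**Working it through.** **1. The plan's own figure.** Power and sample size gives 41.8% and 69%, each moved by 5% towards the other. Read as relative changes:
- control 0.418 × 1.05 = 0.4389
- experimental 0.69 × 0.95 = 0.6555
- difference 0.6555 − 0.4389 = 0.2166, or 21.7 points

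With two-sided alpha 0.05 (assumed, as the article states none) and the pooled-variance formula, this gives 82 per group and 80.1% power, matching the article. Read as percentage points (0.468 vs 0.640, difference 17.2 points), it needs 130 per group, which does not match. So 21.7 points is the difference the sample size implies.

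**2. Which windows are exposed.** Suppose the patient is in hospital at visit *t*, that visit is missed, and the rating at *t* − 3 months was remission.
- *Short stay, later visit attended.* The visit at *t* + 3 covers *t* to *t* + 3, so it rates the stay from *t* onward. The window *t* − 3 to *t*, which holds the start of the admission, is filled by LOCF. Up to 3 of 36 months are wrongly credited.
- *Stay longer than three months.* Visits *t* and *t* + 3 can both be missed. Two windows are filled, up to 6 of 36 months.
- *Admission at month 36.* No later scheduled visit exists, so nothing corrects the last window.

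**3. Do the other provisions close the gap?** Under Participant withdrawal, the final remission assessment is for dropouts (three consecutive misses), and medical files are used for patients who leave treatment but still consent. A patient who misses one visit while in hospital is neither. The models in Statistical analyses test robustness and do not alter the primary result.

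**4. Size for the proportion in remission.** Assume that status is taken at month 36. Let *h* be the share of an arm in hospital and unrated then, and *c* the share of those last rated in remission. Observed remission rises by *h* × *c* in that arm, so

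shrinkage = (*h* control − *h* SEI) × *c*

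None of these inputs is in the document; all are assumptions.

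| *h* control | *h* SEI | *c* | Shrinkage (points) |
|---|---|---|---|
| 2% | 1% | 0.25 | 0.25 |
| 4% | 2% | 0.50 | 1.0 |
| 8% | 4% | 0.50 | 2.0 |
| 8% | 4% | 0.66 | 2.6 |
| equal | equal | any | 0 |

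**5. Effect on power at 82 per group.** With 2%/1% and *c* = 0.25, the difference is 21.4 points and power 79.3%. With 5%/2.5% and *c* = 0.5, it is 20.4 points and 75.5%. These figures keep the plan's post-attrition number. An LOCF analysis would retain more of the 220 randomized, so the power actually available would be higher.

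**The case against.** The strongest reply is that the article never says an in-patient visit is skipped. A reader might infer that in-patients cannot be rated and that the worst outcomes go missing by rule. The document does not support that. The Blinding sentence describes how the blind is kept, and the Discussion restates it without the words that make it universal. No visit window is printed, so a late visit after discharge is not forbidden and its look-back could cover the admission. The next scheduled visit rates the stay from the missed date onward. How such visits are handled may well be in the full protocol. All of this stands, and it confines the point to the three situations above.

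It is also true that LOCF appears only in the abstract, that no admission rate is given, and that the upper value of *c*, two thirds, is well above the planned control remission of 43.9%. The top of the range is therefore generous.

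A reader might go further and want every window with a psychosis admission scored as not in remission. That would override blinded SAPS and SANS ratings with admission decisions made by unblinded clinicians. Because the experimental arm works to avoid hospital use, admission could differ between arms at equal severity, and the rule could favour that arm. This objection also stands and limits the remedy to windows with no blinded rating.

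The reply does not remove the conflict between two rules that the article does state: all assessments off-site without an exception, and LOCF as the primary method. Nothing printed stops remission being carried across a known admission.

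**Conclusion.** The concern holds in limited form. As written, the location rule combined with LOCF can turn a psychosis admission into a carried-forward remission in three situations: the window before a missed date, a stay longer than three months, and an admission at month 36.

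The direction is towards no difference if admissions are more frequent in the control arm, which the document makes plausible but does not quantify. With equal shares the difference is not biased, although both arms' remission rates are overstated. The size is unknown and probably small: about 0.25 to 2.6 of 21.7 points for the proportion, under assumed in-patient shares of 2–8% in controls and 1–4% under SEI, with a quarter to two thirds last rated in remission. For length, up to 3 of 36 months can be wrongly credited per missed visit in an affected patient. It deserves correction because the remedy is cheap and is best fixed before unblinded analysis.

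**What to change.** 1. **Blinding section.** State that a participant in hospital on a visit date may be rated by a blinded assessor by telephone, on the ward, or at a delayed visit whose look-back covers the admission.
2. **Primary outcome rule.** Where a window still has no blinded SAPS/SANS rating and the visit record or Med-Echo shows a psychosis admission in it, do not carry remission forward. Score that window as not in remission, in both arms and for both primary measures. Leave every window with a blinded rating unchanged.

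**Cost.** One sentence in each place. The Med-Echo data are already planned, and consent for database access is sought at entry. Trial status reports all 220 participants randomized and last assessments due in 2015, so the first change helps only the remaining visits; the second can be applied in full at analysis.

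**Downsides.** Ward ratings carry a small risk of unblinding. An occasional admission with only mild ratings would be misclassified. The unrated windows would depend in part on admission decisions by unblinded clinicians.

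### Baseline self-reports are collected after participants know their arm, so the timing cannot prevent self-report bias, and adjusting for them can bias the adjusted and secondary comparisons

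*Protocol article*

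**What the plan says.** All references are to the protocol article.

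- **Timing (Blinding).** "Baseline assessments are conducted as soon as possible, within the first 3-6weeks of randomization, in order to avoid revealing group assignment". The next sentence gives the reason: "This is done to prevent any possibility of bias in self-reports that could influence the comparability between groups".
- **Who knows the arm (Blinding).** "Neither the participants nor case managers and other clinicians can be blinded to the assignment of the treatment condition". The research staff are "blinded to the treatment condition, conduct all assessments outside any of the patient treatment facilities".
- **What happens between randomisation and baseline (Randomization).** After allocation, "patients are asked which condition they would have preferred to be randomized to and if they are satisfied with the allocation they were assigned". Also, "Results of the randomization are communicated to the treatment team such that appropriate transfer decisions may be made". Of the preference and satisfaction answers the section appears to say: "This data will be used as a covariate in case that treatment preference biases outcomes".
- **What is collected at entry.** Table 1 places the randomisation-preference questionnaire at baseline. Secondary outcomes puts subjective quality of life at study entry. Adherence is assessed at every evaluation. Working alliance is on the six-monthly schedule, whose first point I take to be entry.
- **How the data are analysed (Statistical analyses).** The primary tests are an unadjusted Pearson chi-square for the proportion in remission and a t-test or Wilcoxon test for length of remission. Regressions containing every covariate and mediator are additional. Secondary outcomes use regression with covariates and repeated-measures analysis of variance. Covariates are not listed there.

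**The concern.** A baseline value is safe to adjust for, or to measure change from, because allocation cannot have influenced it. Here the entry self-reports come from people who know their arm and, in the control group, may already be in transfer. They are outcomes of allocation, however early they are taken.

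Working alliance is the clearest case. Under Mediating variables it is rated for the respective service providers. Under the experimental intervention the case manager stays the same, while control patients move to other services. At entry the two arms may therefore be rating different people. The protocol also expects this variable to differ between arms. Satisfaction with the assigned arm is by definition a response to allocation, yet it belongs to the data named as a covariate.

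At stake is the treatment-effect estimate in the adjusted regressions and in any secondary analysis that takes the entry value as its starting point. The article also claims a safeguard that the design does not have.

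**Working it through.** **Step 1: sequence of events.** Consent comes first, then randomisation, then the preference and satisfaction questions, with the allocation passed to the treatment team so that transfer can be arranged. The entry assessment also follows randomisation. The article gives no transfer date, so transfer may or may not have begun by then. Knowledge of the arm is enough for the point.

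**Step 2: does early timing deliver the stated property?** Two purposes are run together in the Blinding section. An assessor who sees a patient before care has diverged has fewer cues to the arm, so early timing may protect the assessor's blind. A participant's own report is different: the participant already knows the arm, and no post-randomisation timing can undo that.

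**Step 3: where the values can enter.**
- As covariates: the preference and satisfaction data are named under Randomization. The additional regressions under Statistical analyses could bring in others.
- As time zero: assessments start at entry, so a repeated-measures analysis may take the entry value as its reference.

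**Step 4: what adjustment would do.** The documents give no figure for a shift at entry, so there is none to reproduce. The following is an illustration on assumptions.

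Let *a* be the between-arm shift in the entry score caused by allocation, *r* the slope of outcome on entry score, and *t* the unadjusted difference, all in SD units.

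- Adjusted difference = *t* − *r* × *a*
- Difference in change from entry = *t* − *a*

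With *t* = 0.40 assumed:

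| Shift *a* | Removed, *r* = 0.4 | Adjusted | Removed, *r* = 0.6 | Adjusted |
|---|---|---|---|---|
| 0 | 0 | 0.40 | 0 | 0.40 |
| 0.1 | 0.04 | 0.36 | 0.06 | 0.34 |
| 0.2 | 0.08 | 0.32 | 0.12 | 0.28 |
| 0.3 | 0.12 | 0.28 | 0.18 | 0.22 |

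A simulation with 400,000 participants per setting agrees: adjusted estimates were 0.357 and 0.339 for *a* = 0.1, 0.322 and 0.276 for *a* = 0.2, and 0.278 and 0.222 for *a* = 0.3. The unadjusted difference stayed at about 0.40 throughout (0.395 to 0.405). Change from entry would lose the whole of *a*, that is 0.1 to 0.3 SD over the same range. If allocation shifted entry scores the other way, the sign would reverse and the effect would be inflated.

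**Step 5: does this reach the primary tests?** No. They contain no covariates, and remission is scored on SAPS and SANS by blinded staff. The term *r* × *a* does not arise.

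**The case against.** The best case for the plan is that it keeps its main result clear of this problem. The primary comparison is unadjusted, the raters are blinded, and the Discussion states openly that participants cannot be. Covariate lists are commonly left to the SAP, and apart from preference and satisfaction the article names no entry self-report as a covariate. Working alliance and adherence are listed as mediators, a role in which post-allocation values are proper. Adherence also draws on family report and pill counts, so only its self-reported part is exposed. All of this stands and limits the point to the adjusted and secondary analyses.

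Four stronger readings are tempting, and the article does not support them.

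- *Baseline is measured three to six weeks after randomisation.* The text says as soon as possible, with that window as the outer limit. Symptom ratings look back three months, so at most 6/13 = 46% of the look-back follows randomisation. Treating these ratings as pure follow-up values goes too far.
- *Balance between arms is judged on contaminated values.* Statistical analyses refers to demographic data for that purpose, which knowledge of the arm would hardly change.
- *The loss is a known share of the detectable effect.* The 82 per group under Power and sample size was derived for two remission proportions. Setting assumed shifts on a continuous score against it has no meaning.
- *The primary result is biased.* Step 5 shows that it is not, by this route.

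What the objection does not rescue is the sentence claiming that the timing prevents self-report bias, or the use of satisfaction with the assigned arm as a covariate.

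**Conclusion.** The point holds in a limited form. Entry self-reports on quality of life, working alliance, satisfaction with allocation and adherence are post-allocation values, and the stated reason for the timing is wrong for them. Used as covariates or as time zero, they **can** bias the adjusted and secondary comparisons.

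The size cannot be estimated from the article. It is zero if knowing the arm does not shift the scores. The 0.04 to 0.18 SD for covariate adjustment rests wholly on assumed shifts of 0.1 to 0.3 SD and slopes of 0.4 to 0.6. The unadjusted primary tests and the sample size are not affected.

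**What to change.** Recruitment is complete (Trial status), so the change lies in the analysis and the wording.

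1. Keep the unadjusted primary comparison as it is.
2. In adjusted analyses, restrict covariates to variables fixed before randomisation: the stratification factors sex and substance abuse, duration of untreated psychosis, premorbid adjustment, and end-of-year-two SEI ratings where they exist.
3. Do not adjust treatment-effect estimates for satisfaction with the assigned arm, or for post-randomisation working alliance, quality of life or adherence. Use these only as mediators or as first follow-up values.
4. In repeated-measures analyses, do not take the entry self-report as time zero.
5. Label the entry assessment as post-allocation. Delete the claim that its timing prevents self-report bias; any protection of the assessor's blind can be stated as the reason instead.

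The cost is a few sentences and retrieval of existing records. That year-two ratings are held is an assumption: Recruitment says patients were "approached for their participation between months 21 and 24 of SEI", which describes the approach for consent and not an assessment, although Inclusion criteria refers to remission status at two years. Some patients may lack such ratings, with a small loss of precision in the adjusted models.
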